#### Analysis and Statistical Power

This is a feasibility study, so all analyses will be exploratory, focusing on identifying temporal trends in the self-management mobile app usage and changes in study outcomes and identifying associations between outcomes. Preceding the analyses, we will calculate summary statistics for all measures as well as exploratory plots (histograms and box-plots) for all measures at each time point to identify outliers and potentially spurious values.

Trends over the 4 visits will be examined graphically as a function of time using nonparametrically smoothed plots to help identify when potential effects reach their maximum, plateau, and begin to decrease, which may indicate a time to target for additional interventions. At each time point, we will calculate pairwise correlations between the self-management mobile app usage measures and all study outcomes and examine bivariate scatter-plots with estimated trends for each pair. Distribution-appropriate correlations (Pearson or Spearman) will be calculated as appropriate for each measure and formally tested for statistical significance. These analyses will also be repeated using change from baseline as the outcome rather than the score itself, both as a simple bivariate analysis and using linear regression to model the change as a function of the app usage measures while controlling for baseline values. Analyses will also be repeated using paired *t* tests for differences in HbA_1c_ values from baseline to posttest to measure self-management adherence.

Statistical power will be established based on a small pilot study. A 2010 report on a small randomized controlled trial (RCT) of an mHealth intervention for T1DM in teenagers showed a significant change in self-management adherence from a mean of 3.7 (SD 0.4) at baseline to 3.9 (SD 0.4) at the 12-week follow-up, at an effect size of *d*=0.64 [53]. Given our longer follow-up period (6 months), we expect to observe a larger effect size in our feasibility study because HbA_1c_ has low variability in 3 months [54]. While using a small pilot study to calculate power may not be ideal, it provides a foundation for us to approximate this study’s sample size in order to estimate the critical parameters necessary for this study [55]. The 2010 study also reported no change in HbA_1c_ for the intervention group, but there was an increase in the control group, with SDs ranging from 1.2 to 1.9. Considering that their groups were imbalanced with respect to HbA_1c_ at baseline, it is difficult to project a difference for our study except to note that observing no change in HbA_1c_ may be an improvement over a possible increase in adolescents with usual care. Despite our limited sample size, assuming the use of two-sided tests with a type 1 error rate of 0.05, with 70 participants we will have 80% power to detect relatively modest correlations of .29.

**Table 2 table2:** Survey instruments.

Outcome	Measure	Reliability (α)	Participant
Adherence	Diabetes Behavior Rating Scale	.86	Child or parent
Glycated hemoglobin	Blood test—HbA_1c_	N/A^a^	Child
Social support	Multidimensional Scale of Perceived Social Support	.81	Child or parent
Social support	Diabetes Family Behavior	.79	Child or parent
Self-efficacy	Diabetes Empowerment Scale-Short Form	.84	Child
Quality of life	Pediatric Quality of Life Inventory (general & diabetes specific)	.88	Child
Conflict	Diabetes Family Conflict Scale	.91	Child or parent

^a^N/A: not applicable.

In the event of unanticipated difficulties with recruitment or of attrition of up to 20%, leaving a final sample of 56, the correlation detectable with 80% power increases only slightly to .32. For *t* tests, N=70 provides 80% power to detect an effect size of 0.30, which is smaller than that reported in the RCT, while the effect size detectable with N=56 increases slightly to 0.34 [53].

Additionally, the primary foci of this study include assessment of the following: (1) the effect size of the intervention to power a larger study; (2) feasibility of the app; (3) practicality of data collection procedures; and (4) the ability to implement. We will also perform a post hoc analysis on personal characteristics and satisfaction related to use of the system. At the completion of the study (month 9), we will ask both those who completed the whole intervention and those who withdrew early about their experience with the intervention, including what worked well and what did not. Additionally, we will use the IBM computer usability satisfaction questionnaire to assess usability [56].

The interview data will be analyzed by developing broad code categories based upon perception themes and will serve as a preliminary sorting tool. The researchers will then use thematic analysis and create a list of common perceptions. Once a coding scheme is developed, two coders will perform a pretest by coding randomly selected interview transcripts in order to measure reliability. Coders will work together to reconcile any disagreements; this will allow us to achieve a high level of reliability.

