#### Outcome Measures

Specifically, the aim 2 seeks to determine the feasibility and impact on diabetes of the self-management mobile app among the adolescents and their parents. Demographic information will also be collected including current age, age at diagnosis, race, gender, parental status (ie, mom, dad, stepdad, etc), and method of diabetes treatment (eg, pump).

Hypothesis 1 seeks to demonstrate that adherence to self-management correlates with mobile app usage and a decrease in HbA_1c_. HbA_1c_ data will be collected through the hospital laboratory system. The patient will be provided with a laboratory slip to obtain the baseline HbA_1c_ value. The patient will be instructed to obtain the lab results within 1 week. Once the results are obtained, they will be faxed to the principal investigator via a secure fax line. Adherence will be measured in two ways. First, the participants will complete the Diabetes Behavior Rating Scale [40]. Second, we will use data from the server to determine if they are monitoring blood sugar on schedule and what mechanisms of the app helped the adolescents follow the medical recommendations. For example, we will use time-stamped log-ins, number of sections the user visited, number of individual logs, communication through the app, educational information accessed, and duration of use per log-on.

Hypothesis 2 states that through use of the app, the participants’ self-efficacy [29,41,42], quality of life [43-45], and perceptions of social support [46-48] will improve, and conflict [49] between the child and parent will be reduced from baseline to 3 months. These secondary outcomes are key in helping the adolescents maintain adherence and a normal HbA_1c_ [50-52] and will be measured through surveys. The survey instruments, the participants who will complete them, and reliability for each measure can be found in Table 2.

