One difficulty of using mobile app technology is keeping adolescents engaged with app use over long periods of time. This is also an issue when designing an intervention with outcomes that take 3 or more months to realize significant changes. Data suggests that the majority of user engagement begins to drop after 21 days of use [68,69]. To combat this difficulty, the app includes a points-based customizable avatar. However, it is important to note that researchers anticipate seeing a similar trend in engagement. Another difficulty seen in many studies is problems with recruitment and retention. To combat these difficulties, participants will be contacted frequently, flexible scheduling will be used for participant study meetings, and study newsletters will be sent to participants. In the event of unanticipated difficulties with recruitment or attrition, a final sample of 56 is acceptable [53].

After we have successfully completed this study, the data gathered will be integrated with machine learning in order to modify the app for a wider audience and better tailor the app to the individual user’s behavior and usage preferences. Once completed, we will design and conduct a full-scale RCT. We will also expand the project to iOS (Apple phones). Additionally, we will seek to integrate the data into the patient’s electronic health record.

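### The one named pre-post test is on HbA1c but labelled as adherence, and the effect size it is set against (d=0.64) belongs to an adherence score

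*Protocol article*

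**What the plan says.** The Specific aims box (H1) and Table 2 list adherence and HbA1c as two outcomes. Outcome Measures defines adherence without HbA1c: "Adherence will be measured in two ways. First, the participants will complete the Diabetes Behavior Rating Scale", and "Second, we will use data from the server to determine if they are monitoring blood sugar on schedule".

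Analysis and Statistical Power correlates app usage with every outcome, repeats this on change from baseline, and regresses change on usage with adjustment for baseline. It then adds paired t tests on "differences in HbA_1c_ values from baseline to posttest to measure self-management adherence". No other test of mean change from baseline is named in the article.

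For power, the same section cites a 2010 trial that "showed a significant change in self-management adherence from a mean of 3.7 (SD 0.4) at baseline to 3.9 (SD 0.4"), with d given as 0.64. It expects a larger effect here, because follow-up is longer and HbA1c varies little within 3 months. On HbA1c itself it says: "The 2010 study also reported no change in HbA_1c_ for the intervention group", while the control group rose; SDs ran from 1.2 to 1.9. It concedes that an HbA1c difference is hard to predict. After Table 2 it says that t tests with N=70 have 80% power "to detect an effect size of 0.30, which is smaller than that reported in the RCT"; the figure for N=56 is 0.34.

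**The concern.** Two things are mixed up. The test is run on one primary outcome and described as measuring the other. The detectable effect of that test is then set beside an effect size for the other outcome, which makes the HbA1c comparison look comfortably powered. The argument for expecting more than 0.64 also crosses over: a property of HbA1c is used to enlarge an adherence effect.

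This matters even in an exploratory study. The article names the effect size of the intervention, for powering a larger study, among its main aims, and the Discussion plans a full-scale randomised trial. As written, the plan yields a pre-post result for HbA1c under an adherence label and names no pre-post test for the adherence scale. A reader could take a flat HbA1c result as saying something about adherence that it does not.

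**Working it through.** **Inputs from the article:** two-sided alpha 0.05; 80% power; N=70, or 56 after 20% attrition; stated detectable d of 0.30 and 0.34; adherence 3.7 to 3.9 with SD 0.4 and d=0.64; HbA1c SDs 1.2 to 1.9. **Assumed, because the article does not give it:** a pre-post HbA1c correlation ρ of 0.5 to 0.9, with equal SDs at both visits.

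**1. The plan's own figures.** For a paired t test, the power is that of a noncentral t with n−1 degrees of freedom and noncentrality d√n. A normal approximation is d = (z for alpha + z for power)/√n.
- Two-sided, N=70: (1.960+0.842)/√70 = 0.335; noncentral t gives 0.340.
- Two-sided, N=56: 2.802/√56 = 0.374; noncentral t gives 0.381.
- One-sided, N=70 and 56: noncentral t gives 0.300 and 0.336.

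The stated 0.30 and 0.34 are reproduced only by a one-sided test. At the stated two-sided level they carry 69.7% and 70.5% power. The two-sided values are used below.

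**2. What the HbA1c test can detect.** SD of change = SD × √(2(1−ρ)). Detectable change = d × SD of change. Each cell gives the value for SD 1.2, then for SD 1.9.

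| ρ | SD of change | Detectable, N=70 | Detectable, N=56 | Change equal to d=0.64 |
|---|---|---|---|---|
| 0.5 | 1.20, 1.90 | 0.41, 0.65 | 0.46, 0.72 | 0.77, 1.22 |
| 0.7 | 0.93, 1.47 | 0.32, 0.50 | 0.35, 0.56 | 0.59, 0.94 |
| 0.9 | 0.54, 0.85 | 0.18, 0.29 | 0.20, 0.32 | 0.34, 0.54 |

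So the detectable change is about 0.18 to 0.65 points at N=70 and 0.20 to 0.72 at N=56.

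**3. What the benchmark implies.** If 0.64 applied to HbA1c, two-sided power would exceed 99% at either sample size, and the mean change would be 0.34 to 1.22 points. The article's only HbA1c evidence from that trial is no change in the intervention group. In a single-arm study that group's change is the relevant comparator. At a true change of zero, power equals alpha, 5%.

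**4. Where 0.64 comes from.** The difference in means over the SD is 0.2/0.4 = 0.50, not 0.64. An SD of change of 0.2/0.64 = 0.3125 would give 0.64, with ρ = 1 − 0.3125²/(2×0.16) = 0.69. But the means are rounded to one decimal, so the difference could lie between about 0.1 and 0.3, and 0.256/0.40 is also 0.64. The article does not settle which SD was used.

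**The case against.** The strongest reply is that the paired t test is an add-on. H1 and H2 are worded as associations with app usage, adherence is formally tested through the correlations and the regression of change, and power for correlations is given first. All analyses are called exploratory. The article also warns that an HbA1c difference is hard to predict and that no change might itself be better than usual care. This limits the consequence. It does not repair the adherence label on the HbA1c test or the comparison across outcomes, both of which are in the text.

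Several stronger readings are tempting, and the article does not support them:
- **That adherence goes untested.** It is tested against usage; what is lacking is a named test of its mean change.
- **That leaving the H2 scales without a pre-post test is an error.** In a condensed article, this may be left to a fuller plan.
- **That 0.64 must be standardised by the SD of change.** Rounding leaves this open, as shown above.
- **That the expected larger effect contradicts the Discussion**, where "Data suggests that the majority of user engagement begins to drop after 21 days of use". Usage can wane while effects accumulate, and the article discloses the drop and offers a countermeasure. This is a tension, not a contradiction.
- **That a null HbA1c result would be misreported.** That is speculation.
- **That the cited trial found an HbA1c change of exactly zero, or none in either group.** The statement covers the intervention group only, and may mean no significant change.

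**Conclusion.** The point holds in a limited form. The article states a test under the wrong outcome label and sets its sensitivity against an effect size for another outcome. The 0.64 therefore says nothing about whether HbA1c change can be detected, and low HbA1c variability is no reason to expect an adherence effect above 0.64.

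In HbA1c terms, 80% power requires a mean change of about 0.18 to 0.65 points at N=70 and 0.20 to 0.72 at N=56. These ranges rest on the assumed correlation of 0.5 to 0.9, equal SDs at both visits, and the cited trial's SDs carrying over to this clinic. With the stated 0.30 at N=70, the range would be 0.16 to 0.57, so the conclusion does not depend on whether the test is one- or two-sided. The correction should be made, but the consequence is modest in a single-arm exploratory study.

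**What to change.** - Run the baseline-to-posttest paired test on the Diabetes Behavior Rating Scale as the adherence measure, and separately on HbA1c as glycaemic control.
- Delete the adherence label from the HbA1c test.
- Confine the comparison with d=0.64 to adherence.
- Remove the HbA1c-based reason for expecting an effect larger than 0.64.
- State HbA1c sensitivity in points, with the assumed SD and correlation, using d=0.34 at N=70 and 0.38 at N=56 if tests stay two-sided at 0.05.

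The cost is one further analysis on data already being collected, some rewording, and a power paragraph that reads less favourably for HbA1c.

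### The four detectable effects do not have 80% power with two-sided 0.05 tests: they match one-sided values, and true two-sided power is about 68–71%

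*Protocol article*

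**What the plan says.** Under Analysis and Statistical Power, the protocol article assumes "two-sided tests with a type 1 error rate of 0.05, with 70 participants we will have 80% power to detect relatively modest correlations of .29". For "attrition of up to 20%, leaving a final sample of 56", it says that "the correlation detectable with 80% power increases only slightly to .32". For t tests, it says that "N=70 provides 80% power to detect an effect size of 0.30, which is smaller than that reported in the RCT". After attrition it gives a second t-test value: "while the effect size detectable with N=56 increases slightly to 0.34".

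The same section says that Pearson or Spearman correlations between app usage and outcomes will be formally tested, and that the t tests are paired (baseline to posttest HbA1c). Study Design confirms a single group without controls. The Discussion returns to the smaller sample: "In the event of unanticipated difficulties with recruitment or attrition, a final sample of 56 is acceptable". No one-sided test is mentioned anywhere in the document.

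**The concern.** Sidedness, type 1 error, power and sample size together determine the detectable effect. Here all of them are stated, so each of the four figures can be checked directly, and each is smaller than two-sided testing allows.

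These figures are the article's only quantitative support for its sample size. They also underlie the statement that 56 completers would suffice. A reader who takes 80% power at r=.29 at face value believes that a true association of that size is missed 20% of the time, when the figure is about 30%. Many correlations will be tested, so non-significant results could be taken as stronger evidence against such associations than they are. The article also plans a full-scale randomised trial. The same calculation repeated there would make that trial too small.

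**Working it through.** **Inputs** (Analysis and Statistical Power): two-sided α = 0.05; power 80%; N = 70, and 56 after 20% attrition (70 × 0.80 = 56); stated r = .29 and .32; stated d = 0.30 and 0.34; paired t test in one group. Normal quantiles: 1.960 (two-sided 5%), 1.645 (one-sided 5%), 0.8416 (80% power).

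**1. Trying to reproduce the correlations.** By Fisher z, the detectable r = tanh[(z_α + 0.8416)/√(N − 3)].

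- Two-sided, N=70: tanh(2.8016/√67) = tanh(0.3423) = .3295. Stated: .29.
- Two-sided, N=56: tanh(2.8016/√53) = tanh(0.3848) = .3669. Stated: .32.
- One-sided: .2948 (N=70) and .3289 (N=56).

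The noncentral t calculation uses noncentrality r√N/√(1 − r²) on N − 2 df. It gives .322 and .356 two-sided, and .2875 and .319 one-sided.

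**2. Trying to reproduce the paired t test.** This uses noncentral t with noncentrality d√N on N − 1 df, where d is the mean change divided by the SD of the changes.

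| | N=70 | N=56 |
|---|---|---|
| Stated d | 0.30 | 0.34 |
| Two-sided, 80% power | 0.3396 | 0.3811 |
| One-sided, 80% power | 0.3001 | 0.3364 |

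No figure reproduces two-sided. One-sided with noncentral t, all four do: .2875, .319, 0.3001 and 0.3364 round to .29, .32, 0.30 and 0.34.

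**3. Two-sided power at the stated effects.** By Fisher z, power ≈ Φ(atanh(r)√(N − 3) − 1.960).

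- r=.29, N=70: 0.2986 × 8.185 − 1.960 = 0.484, so Φ = 68.6%.
- r=.32, N=56: 0.3316 × 7.280 − 1.960 = 0.454, so Φ = 67.5%.

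| Stated effect | Fisher z | Simulation (1,000,000 draws) | Noncentral t |
|---|---|---|---|
| r=.29, N=70 | 68.6% | 69.2% | 70.5% |
| r=.32, N=56 | 67.5% | 68.3% | 69.9% |
| d=0.30, N=70 | – | – | 69.7% |
| d=0.34, N=56 | – | – | 70.5% |

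**4. Rounding.** Even at the top of each rounding interval (for example d = 0.345 at N=56, which gives 71.8%), two-sided power reaches only about 72%.

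**5. Completers needed to keep the stated effects, two-sided at 80%.** By Fisher z, N = (2.8016/atanh r)² + 3. For r=.29 this is (2.8016/0.2986)² + 3 ≈ 91.1, so 92. For r=.32 it is 75. By noncentral t, d=0.30 needs 90 and d=0.34 needs 70. The last figure shows the slip plainly: the effect given for 56 completers is the one that 70 completers can detect.

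**The case against.** **The cause is inferred.** The document never mentions a one-sided test, and two-sided tests at about 70% power would give nearly the same numbers. The one-sided match for r at N=56 also depends on the method: noncentral t gives .319, but Fisher z gives .329, which rounds to .33. This stands as a caution about the cause. It does not touch the error, because two-sided testing, 0.05, 80% power and these effects cannot all hold under any of the methods.

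**The replacement correlation depends on the method.** At N=56 the two-sided value is .356 by noncentral t, about .364 by exact calculation and .367 by Fisher z. This is why a range is given and why the method should be named. The value .37 is the standard Fisher z figure and delivers at least 80% power, whereas .36 gives 79.1%.

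**The scale of d is not defined.** If d were divided by the raw SD, the SD of the changes would be the raw SD × √(2(1 − ρ)). The stated figures would then be right when √(2(1 − ρ)) = 0.30/0.3396 = 0.883, so ρ ≈ 0.61, and similarly 0.34/0.3811 = 0.892, so ρ ≈ 0.60. The article states no pre-post correlation, and this reading cannot rescue the two correlation figures, which concern the analysis that addresses both hypotheses.

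**The consequences are limited.** The recruitment section also justifies 70 dyads by similarity to past research. All analyses are called exploratory, no decision rule depends on a p-value, and nothing says that null results will be read as evidence of no association. This largely stands and limits the weight of the point. Even so, the power section itself presents the calculation as a basis for approximating the sample size, and the figures in it are wrong as written.

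**Conclusion.** The concern holds. The four detectable effects are inconsistent with the stated two-sided 5% tests and 80% power. True two-sided power at those effects is about 68–71%, roughly 10 to 12 percentage points short. The correct two-sided values are r about .32–.33 and d = 0.34 at N=70, and r about .36–.37 and d = 0.38 at N=56.

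For the correlations, this rests only on standard power formulas under bivariate normality, confirmed by simulation. For the t tests, it also assumes that d is scaled by the SD of the within-person changes, the usual scale for a paired test. A one-sided setting in the calculation is the likely explanation, but the conclusion does not need it.

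The article's comparison with the earlier trial survives, since 0.34 and 0.38 are still well below 0.64.

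**What to change.** Keep the two-sided tests and N=70. In Analysis and Statistical Power, restate the effects detectable with 80% power as:

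- N=70: r = .33 and d = 0.34
- N=56: r = .37 and d = 0.38

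Name the methods (Fisher z for correlations, noncentral t for the paired test) and say that d is the mean change divided by the SD of the changes. In the Discussion, rest the acceptability of a final sample of 56 on r = .37 and d = 0.38. If the authors prefer to keep the present effects, the alternative is to state the power as about 70%.

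The cost is four numbers and one sentence, with a slightly less favourable statement of sensitivity. No extra participants are needed, and neither the design nor the tests change. Since data collection is already under way, the correction should carry through to the report of results and to the planning of the full-scale trial.

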## Methods

### Study Design

This study has two phases that correspond with the study aims (Textbox 1): app development and pilot testing. In the app development phase, the app will be conceptualized and a prototype will be tested. In Phase 2, the mobile app will undergo pilot testing to determine its feasibility and impact on diabetes self-management. We did not utilize a control group because this is a feasibility study [13].

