#### Study Setting

Recruitment will take place in the Sparrow Hospital’s Pediatric Subspecialty Clinic in Lansing, Michigan, United States. The Sparrow Endocrinology Clinic team consists of 1 registered pediatric dietitian, 1 full-time nurse practitioner, 2 certified diabetes educators, and 2 endocrinologists, all of whom provide diabetes care 4 days per week within the larger subspecialty clinic. All patients are scheduled to come to the clinic every 3 months for care.

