**Adolescents must:**
Have a type 1 diabetes mellitus (T1DM) diagnosis according to the American Diabetes Association practice guidelines [34]Be 10-15 years oldHave had a diagnosis of T1DM for at least 6 months; have glycated hemoglobin>7 [35]Have had at least two outpatient visits in the past 2 yearsBe treated at the local clinic for diabetesBe fluent in EnglishHave a parent or guardian willing to participateBe allowed to use a mobile phone for the studyHave permission from their care team

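### A pilot with no control arm is to supply the intervention effect size for a later RCT, but none of its stated analyses estimates a between-arm effect

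*Protocol article*

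**What the plan says.** All references are to the protocol article.

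- **Aim.** In Analysis and Statistical Power, the first of four primary foci is "the effect size of the intervention to power a larger study". The Discussion says what that study is: "Once completed, we will design and conduct a full-scale RCT".
- **Design.** Study Design: "We did not utilize a control group because this is a feasibility study".
- **Analyses.** Analysis and Statistical Power calls all analyses exploratory. It names plots of trends over the four visits, correlations of usage with each outcome, the same with change from baseline, linear regression of change on usage adjusted for the baseline value, and "paired *t* tests for differences in HbA_1c_ values from baseline to posttest".
- **Expected course without the app.** The same section says of the small earlier RCT that it cites that "there was an increase in the control group, with SDs ranging from 1.2 to 1.9". It adds that a difference is hard to project and that "observing no change in HbA_1c_ may be an improvement over a possible increase in adolescents with usual care".
- **Entry.** The inclusion criteria require adolescents to "have glycated hemoglobin>7". They do not say which measurement qualifies the participant.

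**The concern.** An RCT is powered on the difference between randomised arms. In a single arm, the change from baseline is the app effect plus whatever would have happened without the app. The article gives a reason to think that the second part is not zero, since it expects that HbA1c may rise under usual care. A useful app could then show no change. Selection on a raised HbA1c could work in the opposite direction by adding some regression to the mean.

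If the pilot's number is carried forward as the intervention effect, the RCT could be far too small or needlessly large. The pilot data could not show which.

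**Working it through.** **1. Plan's own figure.** The article gives no between-arm effect and no RCT sample size, so there is nothing to reproduce on this point. Its detectable effect sizes (0.30 at N=70, 0.34 at N=56) concern the pilot's own tests and are not used here.

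**2. What each stated analysis estimates.**

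- Paired t test: mean change within the arm, tested against zero.
- Usage correlations and regressions, with or without baseline adjustment: differences between heavier and lighter users in the same arm. Usage is chosen by the participant, so this is not app versus no app.
- Trend plots, including the month 9 visit after three months off the app (Study Procedures): a within-arm time course.

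None gives a between-arm effect, for HbA1c or any other outcome.

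**3. Consequence for an RCT.** Inputs:

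- SD 1.2 to 1.9, two-sided 0.05 and 80% power, all from Analysis and Statistical Power.
- Assumed: a true between-arm difference of 0.3 HbA1c points, and an untreated change U (positive means a rise).

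Apparent benefit in the pilot = 0.3 − U. Per-arm size = 2 × SD² × (1.96 + 0.8416)² / difference².

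Needed at SD 1.2: 2 × 1.44 × 7.849 / 0.09 = 251.2, so 252 per arm. At SD 1.9: 630 per arm.

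| U | Apparent benefit | n per arm, SD 1.2 | n per arm, SD 1.9 | True power |
|---|---|---|---|---|
| −0.2 | 0.5 | 91 | 227 | 39% |
| −0.1 | 0.4 | 142 | 355 | 56% |
| 0 | 0.3 | 252 | 630 | 80% |
| +0.1 | 0.2 | 566 | 1,417 | 99% |
| +0.2 | 0.1 | 2,261 | 5,667 | about 100% |
| +0.3 | 0 | none follows | none follows | – |

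Check of the first row at SD 1.2: 0.3 / (1.2 × √(2/91)) = 1.69; 1.69 − 1.96 = −0.27; normal probability 0.39.

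**4. How much regression to the mean?** This depends on which value qualifies the participant. Assume a clinic mean of 8 to 9 and a correlation ρ between visits of 0.70 to 0.85.

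- *If the baseline value itself qualifies:* expected fall = (1 − ρ) × SD × φ(a)/(1 − Φ(a)), with a = (7 − mean)/SD. Smallest: mean 9, SD 1.2, ρ 0.85 gives 0.15 × 1.2 × 0.1045 = 0.02. Largest: mean 8, SD 1.9, ρ 0.70 gives 0.30 × 1.9 × 0.496 = 0.28.
- *If an earlier value x qualifies:* with equal correlation between all occasions, baseline and follow-up both have expectation mean + ρ(x − mean), so the expected fall from baseline is zero. A fall remains only if correlation decays with time.

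The described sequence fits the second case better. Eligibility is settled by a screening questionnaire (Sample and Recruitment of Participants), and Visit 1 is booked during screening (Study Procedures). The baseline laboratory value is obtained from a slip within a week (Outcome Measures).

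**The case against.** **A feasibility pilot needs no control arm, and the article says openly that it has none.** This stands. It also calls its analyses exploratory and admits that a difference is hard to project. The design is not the fault. These caveats sit beside a first-listed aim that the design cannot meet, and they do not change that aim.

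**The article names neither the outcome nor the contrast behind the effect size.** This also stands. The effect size that it discusses from the earlier RCT (d=0.64) is for adherence, not HbA1c. A reader might infer that the later trial will be sized from HbA1c change against zero. No sentence commits to that. The point does not need it, because no stated analysis of any outcome yields a between-arm effect.

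**The paired t test is not the only look at change.** Correct. There are baseline-adjusted regressions and an off-app visit. They add information, but all within one arm.

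**Details may be in a fuller document.** Possibly. But the aim, the design and the analyses are all stated here, and they do not fit together.

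**A reader might infer that entry above 7 will make a useless app look effective.** The documents do not support this. The text suggests that the qualifying value precedes the Visit 1 test, in which case regression to the mean is probably small, and the possible usual-care rise acts in the other direction.

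**Conclusion.** The point holds in a limited form: the pilot cannot estimate the intervention effect that a later RCT would be powered on, although the article lists that effect first among its foci. Its own remark about usual care shows why change against zero is not a valid reference.

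The sign of the error is unknown, so the conclusion is that the effect is not identified, not that it will be overstated. In the illustration, an untreated change of 0.2 points either way moves the RCT from the 252 per arm needed to 91 or 2,261 at SD 1.2, and from 630 to 227 or 5,667 at SD 1.9. Only the SDs, the error rate and the power come from the article. The true difference of 0.3 and the untreated changes are assumptions, and the documents give no figure for either. The feasibility, data-collection and implementation aims are unaffected.

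**What to change.** In Analysis and Statistical Power:

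1. Replace the intervention effect size in the first focus with what this design can estimate: SD of the outcomes and of change, within-person correlation, retention and app usage.
2. Report the pre-post change with a confidence interval, labelled descriptive and not as an effect of the app.
3. State that the RCT will be powered on a minimum important difference or on controlled data.

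This needs no new data or visits, so it can be done with the pilot under way. The cost is that the pilot no longer claims to supply an intervention effect size.

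Modelling each participant's earlier clinic values as their own control may look attractive, since Study Setting says "All patients are scheduled to come to the clinic every 3 months for care". I would not do it. Entry guarantees only two visits in two years. If the qualifying value is among those extracted, it was selected to be high: by the formula in step 4, the value before it is expected to be 0.02 to 0.28 lower with no true trend. Projecting that false rise would flatter the app, and the result would still not be a between-arm effect.
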